## Abstract

**Introduction:**

Clinical practice guidelines recommend against the routine use of psychotropic medications in residential aged care facilities (RACFs). Knowledge brokers are individuals or groups who facilitate the transfer of knowledge into practice. The objective of this trial is to evaluate the effectiveness and cost-effectiveness of using knowledge brokers to translate Australia’s new Clinical Practice Guidelines for the Appropriate Use of Psychotropic Medications in People Living with Dementia and in Residential Aged Care.

**Discussion:**

The EMBRACE trial investigates a novel guideline implementation strategy to improve the safe and effective use of psychotropic medications in RACFs. We anticipate that the findings will provide new information on the potential role of knowledge brokers for successful and cost-effective guideline implementation.

**Trial registration:**

Australian New Zealand Clinical Trials Registry (ANZCTR): ACTRN12623001141639. Registered 6 November 2023 — retrospectively registered, https://www.anzctr.org.au/TrialSearch.aspx.

**Supplementary Information:**

The online version contains supplementary material available at 10.1186/s13012-024-01353-z.

Contributions to the literature
This trial is one of the first to directly compare different guideline implementation strategies to improve concordance with clinical practice guidelines in residential aged care facilities.This trial will utilise a helix-counterbalanced study design to simultaneously deliver and evaluate multiple strategies to improve appropriate use of psychotropic medications across residential aged care facilities.This trial will evaluate a novel role for pharmacists as system-level knowledge brokers in residential aged care facilities.If successful, the guideline implementation strategies may be applicable to other therapeutic areas and contexts to improve the quality use of medications for residents living in residential aged care facilities.

## Background

Persistent high rates of psychotropic medication use in residential aged care facilities (RACFs) remain a concern for residents, caregivers and other stakeholders. This is despite a lack of evidence supporting benefits of psychotropic medication but well-documented risks of harm. More than 60% of Australian RACF residents use regular psychotropic medications, with 41% prescribed antidepressants, 22% antipsychotics and 22% benzodiazepines on a regular basis [1]. Psychotropic medication prevalence is also highly variable, with a study across 27 RACFs in the state of Victoria reporting antipsychotic prevalence ranged from 0 to 95% (mean 32%) and antidepressant prevalence ranged from 10 to 89% (mean 48%) [2].

The American Psychiatric Association [3], European Academy of Neurology [4] and Australian Clinical Practice Guidelines and Principles of Care for People with Dementia [5] recommend avoiding antipsychotics in people living with dementia. Evidence suggests antipsychotics are associated with increased risk of cardiovascular and cerebrovascular events, falls and death [6, 7]. Benzodiazepines are associated with minimal and short-term improvements in sleep disturbances but also with an increased risk of hip fracture [8] and falls [9]. Antidepressants have uncertain benefits in people living with dementia and have been associated with adverse events including dry mouth, dizziness and falls [10].

In October 2019, Australia’s Royal Commission into Aged Care Quality and Safety identified overreliance on psychotropic medications for chemical restraint as one of three areas for immediate action [11]. The National Health and Medical Research Council (NHMRC) Dementia Centre for Research Collaboration subsequently commissioned new Australian Clinical Practice Guidelines for the Appropriate Use of Psychotropic Medications in People Living with Dementia and in Residential Aged Care (the Guidelines) [12]. The Guidelines were developed by a multidisciplinary 18-member Guideline Development Group, supported by a Stakeholder Advisory Committee comprising government agencies, professional groups, aged care provider organisations and quality improvement organisations. The Guidelines were developed using an integrated knowledge translation process in collaboration with five aged care provider organisations in Queensland, South Australia, Western Australia and New South Wales [13, 14]. Ongoing focus groups with these organisations suggested that innovative guideline implementation strategies would be needed to fully implement guideline recommendations and good practice statements.

Poor implementation of guideline recommendations is recognised as a barrier to reducing medication-related harm [15]. There is emerging interest in engaging knowledge brokers to support guideline implementation [16]. Knowledge brokers are individuals or groups that help to move knowledge from those who create the knowledge (e.g. guideline developers) to those that use the knowledge (e.g. health care professionals) [16]. Knowledge brokers act as knowledge managers, linking agents and capacity builders [16]. The role of a knowledge broker is consistent with the Australian Government’s recent announcement of AUD $345.7 million over 4 years for on-site embedded pharmacists in all Government-funded RACFs to improve medication safety [17]. Quality Use of Medicines (QUM) and Medicines Safety is also Australia’s newest National Health Priority Area [18]. In recognition that evidence-based recommendations alone are not sufficient to ensure guideline-concordant appropriate medication use, we developed a series of data-driven knowledge translation strategies for implementing the new Guidelines.

The objective of this trial is to evaluate the effectiveness and cost-effectiveness of using knowledge brokers to translate Australia’s new Clinical Practice Guidelines for the Appropriate Use of Psychotropic Medications in People Living with Dementia and in Residential Aged Care. Guideline implementation using knowledge brokers will be compared to guideline implementation through the following: (1) distribution of the Guidelines and supporting materials and (2) pharmacist-led QUM education activities.

## Methods

### Design

The *E*vidence-based *M*edication knowledge *B*rokers in *R*esidential *A*ged *C*ar*E* (EMBRACE) trial is a 12-month helix-counterbalanced randomised controlled trial [19]. The trial will examine three different guideline implementation strategies (Fig. 1). These strategies will be evaluated across the three psychotropic medication contexts included in the new Guidelines (antipsychotics, benzodiazepines and antidepressants) [12]. All participating RACFs will receive all implementation strategies but for different medication contexts (Table 1, Fig. 1). This trial will involve RACF-level interventions that will not involve the investigators collecting resident-level identifiable data.

**Fig. 1 Fig1:**
[figure not shown]
Helix counterbalanced design illustrating context area-by-intervention level combinations for three groups of residential aged care facilities (square, circle and triangle). This Figure was adapted with permission from Sarkies et al. Implementation Science 2019;14:45. Abbreviations: QUM, quality use of medicine

**Table 1 Tab1:** Intervention combinations delivered for each RACF group

Group	Levels	Knowledge translation strategy to medication context area
Group A RACF	**Level 1**	Distribution of hard copy and electronic guideline on *antidepressants*
	**Level 2**	Distribution of the Guidelines and QUM education sessions on *benzodiazepines*
	**Level 3**	Knowledge broker led local action plans, QUM education sessions and distribution of the Guidelines on *antipsychotics*
Group B RACF	**Level 1**	Distribution of hard copy and electronic guideline on *antipsychotics*
	**Level 2**	Distribution of the Guidelines and QUM education sessions on *antidepressants*
	**Level 3**	Knowledge broker led local action plans, QUM education session and distribution of the Guidelines on *benzodiazepines*
Group C RACF	**Level 1**	Distribution of hard copy and electronic guideline on *benzodiazepines*
	**Level 2**	Distribution of the Guidelines and QUM education sessions on *antipsychotics*
	**Level 3**	Knowledge broker led local action plans, QUM education session and distribution of the Guidelines on *antidepressants*

Abbreviations: *RACF*, residential aged care facility; *QUM*, quality use of medicine

In advance of the trial, the Project Management Team met with each participating aged care provider organisation’s leadership team to discuss the trial design and delivery. Design of this trial was also informed by a series of foundational activities including the following:An integrated knowledge translation process involving an ongoing series of focus groups with aged care provider organisations to develop the new Clinical Practice Guidelines for the Appropriate Use of Psychotropic Medications in People Living with Dementia and in Residential Aged Care [12, 14].In-depth semi-structured interviews and focus groups (*n* = 33) involving RACF managers, prescribers, pharmacists, nurses, aged care workers, residents, carers and other key stakeholders at participating aged care provider organisations to assess each aged care provider organisation’s existing quality improvement processes [20].Fifteen semi-structured interviews with early adopters of Australia’s embedded on-site aged care pharmacist model to understand potential synergies with our knowledge broker role and to inform the development of knowledge broker training [21].Systematic review of the published literature on the roles and effectiveness of knowledge brokers in implementing clinical practice guidelines [16].

### Setting

The trial will be conducted in up to 19 RACFs operated by four aged care provider organisations in the states of Victoria, New South Wales, Western Australia and Queensland. The four aged care provider organisations are non-government, independent and not-for-profit organisations. Australian RACFs provide supported accommodation for people with care needs that can no longer be met in their own homes and are synonymous with long-term care facilities and nursing homes in other countries [22, 23]. Approximately, two thirds (65%) of residents in Australian RACFs are women, and 58% of residents are aged 85 years and over [24]. In Australian RACFs, medications are mostly prescribed by visiting medical practitioners, dispensed by off-site community pharmacies and administered by registered nurses or credentialled aged care workers [25]. Each aged care provider organisation’s leadership team will be responsible for identifying the specific RACFs operated by that organisation to take part in the trial. The trial protocol conforms to the Standard Protocol Items: Recommendations for Interventional Trials (SPIRIT) guidelines [26, 27] (Additional file 1). The trial has been registered with the Australian and New Zealand Clinical Trials Registry (ANZCTR) (registration no.: ACTRN12623001141639, date registered: 06/11/2023). The application for trial registration was submitted on the 20th of September 2023 (as shown on the ANZCTR trial registration site) prior to randomisation of RACFs, but the trial was not formally registered until 6th November 2023. There were no changes to the trial protocol between the submission date (20th of September 2023) and the registration date (6 November 2023).

### Governance and consultation

The trial will be overseen by the Project Management Team comprising the lead investigators and project manager. During the trial, the Project Management Team will meet with the aged care provider organisation representatives and knowledge brokers monthly or more frequently if required to monitor the data collection and conduct of the trial and to identify any potential adverse events. Meetings will mostly be conducted via video-teleconferencing (e.g. Zoom), with face-to-face meetings organised if needed.

The trial will be supported by a stakeholder group comprising government agencies (Aged Care Quality and Safety Commission, Australian Commission on Safety and Quality in Health Care), professional groups (Royal Australian and New Zealand College of Psychiatrists, Australian and New Zealand Society of Geriatric Medicine, Australian College of Nursing, Pharmaceutical Society of Australia, Pharmacy Guild of Australia), and an advocacy body (Dementia Australia). The stakeholder group will meet annually for the duration of the trial including at implementation, evaluation and dissemination stages. A Data Safety Monitoring Board will meet as and when required during the trial. It will involve an independent group of healthcare professionals with relevant clinical expertise (e.g. general practitioner, geriatrician, nurse, pharmacist).

### Randomisation and blinding

This trial will involve RACF-level interventions, and individual residents will not be recruited to participate. The unit of randomisation will be RACFs. Once potential availability of specific RACFs is determined by each aged care provider organisation, the RACF manager or an authorised representative of the aged care provider organisation will be provided with a written explanatory statement, and informed consent to participate will be obtained.

RACFs will be matched into blocks of three based on the aged care provider organisation and geographical location. One RACF within each block of three will be randomised to groups A, B, or C and receive three levels of intervention for a combination of implementation strategies and medication contexts (Table 1). Randomisation will be performed by an independent epidemiologist using a computerised random number generator within SAS (SAS Institute, Cary, NC, USA).

Following randomisation, each aged care provider organisation leadership team and their knowledge brokers will be notified of group allocations for each participating RACF within their organisation. Due to the nature of the trial, it will not be possible to blind the leadership team or knowledge brokers. Partial disclosure will be implemented for RACF nurses, aged care workers and visiting pharmacist and medical practitioners at each RACF. These clinicians and staff will be aware of the trial objectives and implementation strategies but will be blinded to the RACF group allocation. The availability of the knowledge broker service will be communicated via letters, posters and notice boards. Residents and their families will be made aware of the trial through distribution of notices and posters at each RACF. The primary outcome will be analysed by a blinded statistician or epidemiologist. The Project Management Team will not be blinded to the group allocations.

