### Sample size and power

The sample size of 19 RACFs was deemed to have sufficient statistical power. To estimate the statistical power of the helix, counterbalanced, three-strategy, and three-context area (medication type) trial design, we performed 1000 Monte Carlo simulations using Stata/SE Statistical Software: Release 17.0 (StataCorp. 2021). The sample size analysis was conducted at the RACF level based on the primary outcome (i.e. proportion of RACF-level Guideline concordant use of antipsychotics, benzodiazepines and antidepressants). The sample size was based on conducting analysis using a linear mixed model employing fixed, categorical factors for medication type and guideline implementation strategy and RACF as a random intercept. We assumed a minimum important effect size of an absolute change in the proportion of concordant medication category takers of 5% for the level 2 strategy relative to level 1 strategy and of 15% for the level 3 strategy relative to level 1 strategy. Given these assumptions, our sample size of 19 RACFs provides > 99% power to detect the absolute change in proportion of concordant medication category takers of 15% and 81% power to detect the absolute change in proportion of 5%.

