### Analysis plan

#### Effectiveness analysis

All primary analyses will be conducted using the intention-to-treat (ITT) principle. Level 3 intervention will be compared to level 1 and level 2 at the 6-month time point as a primary outcome (Table 4).

Per protocol analysis will also be undertaken with the per protocol set including all RACFs without a major protocol deviation. Major protocol deviations may include, but are not limited to, the following:Loss of knowledge brokerIncomplete delivery of intervention (e.g. local action plans, QUM service)

We anticipate that the primary analysis will be conducted using a linear mixed model treating the RACF as a random effect, with the strategy level and medication contexts as fixed effects. Multiple imputation will be used to impute missing covariate values where necessary. Data will be analysed using Stata/SE Statistical Software: Release 17.0 (StataCorp. 2021).

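### The stated primary model omits the matching by provider: provider-by-drug-class differences that the triplets cancel stay in the error term, so intervals are too wide if such differences exist

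*Protocol article*

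**What the plan says.** Under Randomisation and blinding: "RACFs will be matched into blocks of three based on the aged care provider organisation and geographical location". One RACF per block is then randomised to each of groups A, B and C, and Table 1 assigns each group a different pairing of strategy level with drug class.

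Under Effectiveness analysis, the anticipated primary model is a "linear mixed model treating the RACF as a random effect, with the strategy level and medication contexts as fixed effects". Sample size and power uses the same terms: a "linear mixed model employing fixed, categorical factors for medication type and guideline implementation strategy and RACF as a random intercept". Neither model has a term for block, provider or location, alone or crossed with medication context.

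The Discussion argues that adjustment for RACF characteristics is unnecessary, since every RACF contributes data under every strategy. The Setting section gives the size as "up to 19 RACFs operated by four aged care provider organisations".

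**The concern.** An analysis should normally reflect the restrictions used in the randomisation; otherwise its standard errors describe a design that was not run. Here the Discussion's argument covers anything that shifts all three drug classes in a RACF equally, because the RACF intercept removes it. It does not cover a provider that does well on antipsychotic review and poorly on benzodiazepine consent.

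Such differences are plausible. Medication Advisory Committees implement medication policies, the indicators in Tables 5 to 7 concern consent, review dates and class-specific monitoring, and each provider employs or contracts its own data collectors. At stake is precision in a trial of at most 19 units that claims only 81% power for its smaller effect.

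**Working it through.** **Inputs from the article.** Up to 19 RACFs, four providers, three contexts and three levels per RACF. Assumed effects are "5% for the level 2 strategy relative to level 1 strategy and of 15% for the level 3 strategy relative to level 1 strategy". The stated power is: "our sample size of 19 RACFs provides > 99% power to detect the absolute change in proportion of concordant medication category takers of 15" percentage points, and "81% power to detect the absolute change in proportion of 5" points.

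**Assumptions, not in the article.** Two-sided 5% test; split of RACFs over providers; share ρ of within-RACF variance that lies between providers by drug class (0, 10, 25 or 50%). RACF was fitted as fixed, which gives the same strategy contrasts in the balanced design and nearly the same with one extra RACF.

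**1. The stated power.** No SD is given, so it cannot be reproduced independently, but the two figures can be checked against each other.
- Residual df = 57 observations − (19 RACF + 2 context + 2 strategy parameters) = 34.
- SE of a level contrast ≈ σ√(2/19). The σ that gives 81% power at 5 points is 0.0527, so SE = 0.0171 and 0.05/0.0171 = 2.92.
- At 15 points, 0.15/0.0171 = 8.8, which gives power above 99.9%.

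The two stated powers agree with each other at a within-RACF SD of about 5.3 points.

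**2. Why the differences cancel.** Let u(class) be a provider's deviation for each class. In one triplet, level 2 is met by benzodiazepines (A), antidepressants (B) and antipsychotics (C). Level 1 is met by antidepressants (A), antipsychotics (B) and benzodiazepines (C). Both sums equal u(benzodiazepines) + u(antidepressants) + u(antipsychotics), so the level 2 minus level 1 difference contains no u. Level 3 behaves the same way. The true variance of the contrast is therefore 2σ²(1−ρ)/n.

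**3. What the stated model reports.** Take six full triplets over providers of 6/6/3/3 (18 RACFs, 32 df).
- Expected provider-by-class sum of squares left in the residual: 2ρσ²(18 − 90/18) = 26ρσ².
- Expected residual mean square: σ²(1 − ρ + 26ρ/32) = σ²(1 − 0.1875ρ).
- Reported SE / true SE = √[(1 − 0.1875ρ)/(1 − ρ)].

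| ρ | Ratio, 18 RACFs | Ratio, 19 RACFs (6/6/3/4) |
|---|---|---|
| 0 | 1.00 | 1.00 |
| 10% | √(0.98125/0.90) = 1.04 | 1.04 |
| 25% | √(0.95313/0.75) = 1.13 | 1.12 |
| 50% | √(0.90625/0.50) = 1.35 | 1.32 |

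The 19-RACF column is the same calculation on the full design matrix; the extra RACF makes the cancellation slightly incomplete.

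**4. Simulation.** 19 RACFs, total within-RACF SD 0.053, 5-point effect, 3000 replicates. Each cell gives the stated model, then the model with provider by context.

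| ρ | Mean 95% CI width | Coverage | Power |
|---|---|---|---|
| 0 | 0.0689 / 0.0697 | 94.9% / 94.8% | 81% / 79% |
| 10% | 0.0684 / 0.0661 | 96.0% / 94.8% | 83% / 85% |
| 25% | 0.0672 / 0.0602 | 97.3% / 95.0% | 84% / 90% |
| 50% | 0.0655 / 0.0495 | 98.8% / 94.7% | 90% / 98% |

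A separate null simulation (split 6/6/4/3) gave a type I error for the stated model of 3.8%, 2.6% and 1.3% at 10, 25 and 50%. Adding provider by context brought it back to about 5%.

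**5. Cost of the term.** Four providers by three contexts add 3 × 2 = 6 parameters, so df fall from 34 to 28. With ρ = 0, calculated power goes from 81% to 80%.

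**The case against.** **The analysis plan may settle it.** The model is introduced as anticipated, and the mention of imputing covariates suggests that further terms may follow. That is fair, and it makes the change easy. But the article does state a model and powers the trial on the same terms, so this is a stated choice and not only an omission.

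**Main effects are already handled.** This stands. A reader might infer that the analysis ignores provider and location altogether. It does not: the RACF effect contains both, and only the interaction with drug class is left out.

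**The size is unknown.** This also stands. A reader might conclude that the intervals will be too wide by some definite amount. The article gives no provider-by-class variance, and at a 10% share the effect is small.

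**The tests may not be conservative.** Brokers are employed per provider, so strategy effects may also vary by provider. With an assumed SD of 1.5 points for that variation and inference meant beyond these four providers, null rejection was about 7% under the stated model and about 9% with the added term. A blanket claim of conservatism is therefore not supported, and the fix must say to whom the inference applies.

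**Baseline adjustment does most of the work.** Assume that half of the non-provider variance persists from baseline. At a 25% share the SE is then 0.0167 under the stated model, 0.0135 with baseline and 0.0131 with both. At 50% it is 0.0163, 0.0113 and 0.0107. The added term then gains only about 3 to 5%.

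**Nineteen is not a multiple of three.** A reader might call this a design error. The article says "The trial will be conducted in up to 19 RACFs", and one RACF outside a full triplet leaves the pattern essentially unchanged. It is a minor detail.

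**Conclusion.** The point holds conditionally. The stated model does not follow the matched randomisation for provider-by-drug-class differences. If those differences exist and strategy effects are common across providers, the standard error is about 4 to 5% too large at a 10% share of within-RACF variance, about 12% at 25% and about a third at 50%. At 0% there is no effect. These figures rest on an assumed split over providers and on the share itself; the SD back-solved from the stated power sets the scale for the widths and power.

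The strategy estimate is not biased. What is lost is precision: at a 25% share, roughly 84% power against 90% for the 5-point effect. Severity is low to moderate.

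**What to change.** Add provider organisation by medication context as fixed effects to the primary model, and state that inference is to the four participating providers. Provider is more practical than triplet because 19 RACFs do not form complete triplets; location within provider would remain unmodelled in its interaction with class.

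The cost is one line in the analysis plan and 6 degrees of freedom (34 to 28), which is about one point of power if providers do not differ by class. If baseline concordance is also to be a covariate, specify both together and expect a smaller gain from this term. The decision should be fixed before unblinded outcome data are examined.
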